#### Selection of families.

In each selected settlement, up to 50 families will participate in the study, chosen through simple random sampling from official lists provided by local associations or INCRA. The inclusion criteria for families are: (i) residing in the settlement; and (ii) having an adult household member available to respond to the questionnaire; and (iii) providing voluntary informed consent (ICF). Families will be excluded if: (i) they do not meet the residency requirement; (ii) they refuse or cannot provide consent; or (iii) communication barriers make the interview unfeasible.

#### Qualitative saturation criterion.

Qualitative data collection will follow the principle of theoretical saturation [37], assessed iteratively by the analysis team during coding. As a guiding strategy, we will consider saturation reached when two or more consecutive interviews or focus groups no longer generate new relevant codes. However, given the high heterogeneity of Amazonian settlements (e.g., floodplains, mining zones, forest-based communities), this criterion will be applied flexibly. Data collection may be extended in specific contexts if new themes continue to emerge or if settlement-specific dynamics require further exploration. To ensure robustness, saturation will be evaluated both within settlement types and across municipalities and will be triangulated with survey findings and field observations to confirm completeness.

0.30	NA	NA	NA

These results demonstrate that the proposed sample is well suited to detecting effects of practical relevance under low to moderate intraclass correlation, while also providing a transparent benchmark for interpreting potential null findings in more highly clustered settings. Consistent with this sensitivity analysis, if logistical constraints arise during fieldwork, priority will be given to maximizing the number of settlements rather than increasing the number of families per settlement, as this yields greater power for between-cluster comparisons. Full simulation scripts will be made available in the project’s OSF repository to ensure computational transparency and reproducibility [38].

### Description of all processes, interventions, and comparisons

Data collection will be carried out sequentially in two integrated phases, as detailed below. The methodological design was refined following a pilot study conducted in the municipality of Marabá (PA), with the resulting adjustments described to ensure process transparency.

#### Phase 1: Secondary data and political-institutional context analysis.

This phase will focus on building a comprehensive diagnosis of the municipal context. It will involve, first, Climate Risk Assessment, through the compilation and analysis of secondary climate indicators widely recognized in the literature (e.g., temperature, precipitation, extreme events) from sources such as the National Institute of Meteorology (INMET) and the National Institute for Space Research (INPE), to characterize the exposure and sensitivity of the sampled municipalities. Second, Public Policy Mapping, through the identification and documentary analysis of municipal and state-level public policies related to climate change, agriculture, and rural development. This will include the analysis of master plans, laws, and decrees, with attention to both actions explicitly labeled as “climate-related” and sectoral actions with indirect impacts on adaptation and mitigation (e.g., sanitation, civil defense, family farming) [26]. Third, Public Budget Audit, applying a data mining methodology to municipal transparency portals [33,34], which allows categorization and quantification of public expenditures directly or indirectly related to the climate agenda, thus overcoming the limitation of expenditures formally tagged as “climatic” [39].

#### Phase 2: Primary data collection with key stakeholders.

This phase will capture the perceptions, experiences, and strategies of local actors through three instruments: (i) Household Surveys: administration of a structured questionnaire to a sample of families in each settlement, collecting socioeconomic, productive, climate perception, and adaptation strategy data (S1 File); (ii) Focus Groups with Community Leaders in each settlement type: group discussions to obtain a consolidated view of vulnerabilities, conflicts, and collective adaptation strategies in the settlements, as well as to validate contextual information (S2 File); (iii) Semi-Structured Interviews with Public Managers: interviews with municipal technicians and secretaries to understand perceptions, implementation challenges, and the articulation of climate policies from the perspective of local government (S3 File).

#### Post-pilot methodological adjustments.

Testing the instruments in Marabá (PA) resulted in crucial refinements. For Phase 1, the policy and budget analysis methodology was expanded to systematically capture implicit climate actions, as the pilot revealed that most municipal climate responses are driven by sectoral policies (e.g., agriculture, infrastructure) not explicitly labeled as climate related. For Phase 2, the household survey was adapted to include specific modules for riverine and floodplain communities, capturing climate impacts (e.g., changes in flood cycles, river-based access). The interview guide with managers was revised to replace technical jargon with more accessible terms, reflecting the fact that many municipalities lack a consolidated formal framework for climate policy.

### Data analysis plan

Data analysis will follow a sequential explanatory mixed-methods strategy (QUAN → QUAL) [40], in which the initial quantitative analysis will provide an overall picture to be subsequently deepened and contextualized by qualitative investigation. Triangulation of data from different sources (quantitative, qualitative, and secondary) will be employed to validate and enrich the findings, ensuring a robust understanding of the factors that influence climate resilience [41]. All analyses will be performed using R software (version 4.3.0 or higher) for the quantitative component and NVivo software (version 14 or higher) to support the organization and coding of qualitative data.

#### General Strategy and Integration.

The analysis will occur in three main stages, corresponding to the data sets, culminating in an integration phase: (i) Secondary Data and Municipal Context Analysis, to characterize the macro context. (ii) Quantitative Primary Data Analysis (Survey), aimed at identifying patterns and testing hypotheses at household and community levels. (iii) Qualitative Primary Data Analysis (Interviews and Focus Groups), to explore causal mechanisms, perceptions, and nuances. (iv) Finally, integration and triangulation, with a synthesis of the findings to answer the research objectives.

#### Secondary data and municipal context analysis.

The analysis of secondary data will proceed in three integrated steps to construct key municipal-level variables. First, a Municipal Climate Vulnerability Index (MCVI) will be created by compiling secondary indicators of exposure, sensitivity, and adaptive capacity from sources including AdaptaBrasil, MCTI, IBGE, and INPE. These indicators will be harmonized by converting to per capita measures where appropriate, standardized (z-scores), and aggregated through Principal Component Analysis (PCA) [42]. Second, municipal climate change plans will be assessed using categorical content analysis to generate a plan quality score. Third, a public expenditure audit, employing text mining of municipal transparency portals, will be conducted to identify and quantify climate-related budgets.

To ensure robustness, a multi-step strategy will address data quality challenges. For the MCVI, discrepancies or missing values will be handled using imputation techniques, with sensitivity analyses conducted to assess the impact on the index. Furthermore, all secondary data – including the budget analysis and plan documentation – will be cross-checked against municipal transparency portals and triangulated with qualitative data from interviews and focus groups to ensure contextual accuracy.

Finally, the plan quality scores, and budget allocations will be combined to create a Municipal Climate Engagement Typology (e.g., High, Medium, Low). Both the MCVI and this engagement typology will be incorporated as contextual variables in the multilevel models.

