**Socioeconomic and Livelihoods**	PH2: Household income diversification (agricultural, extractive, non-agricultural) is positively associated with higher perceived climate resilience and greater adoption of adaptation actions.	Diversification reduces dependence on a single activity vulnerable to climate events, enabling the absorption of shocks and the reallocation of resources [22,23]
**Demographic and Social Capital**	PH3: Multigenerational demographic composition and participation in community organizations are positively correlated with the adoption of a more diversified portfolio of adaptation strategies (both traditional and innovative).	Intergenerationality facilitates the transmission of traditional knowledge, while social organization facilitates access to information, resources, and external policies [24,25].
**Institutional and Public Policies**	PH4: The existence and implementation of participatory public policies on climate and bioeconomy explicitly at the municipal level are associated with higher adaptive capacity reported by communities and greater productive diversification based on socio-biodiversity.	Well-designed and participatory policies provide the resources, incentives, and structures necessary for communities to implement effective adaptation strategies at scale [26,27].
**Bioeconomy and Climate**	PH5: Engagement in bioeconomy value chains (particularly processing and certification) is positively associated with higher household income levels and the adoption of climate mitigation and adaptation practices.	Value addition and access to differentiated markets create economic incentives for conservation and for investment in sustainable and resilient practices [28,29].

The approach integrates public policy indicators (e.g., existence of mitigation and adaptation plans, climate budget) with community perceptions, allowing for a broader analysis of ongoing impacts and adaptation strategies. The data collected under this protocol aims to test hypotheses based on (i) spatial patterns; (ii) socioeconomic patterns; (iii) demographic patterns; (iv) institutional/political patterns; and (v) bioeconomy/climate patterns.

Table 1 summarizes the main hypotheses guiding this work.

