Income and Livelihood Diversification Index (ILDI): a continuous score (0–1) that synthesizes the distribution of agricultural, extractive, and non-agricultural income. This index is adapted from standard diversification measures widely used in livelihood and rural development research (e.g., Herfindahl–Hirschman approaches [30]). *Expected direction*: higher values will be associated with greater diversification of adaptation actions (PH2).Climate Vulnerability Perception Scale (CVPS): a reflective scale (1–5) constructed from Likert-type items assessing perceived frequency, severity, and impacts of climate-related events. This scale is adapted conceptually from prior work on climate risk perception but operationalized specifically for Amazonian rural contexts. Internal consistency and dimensionality will be assessed through Cronbach’s alpha [31] and confirmatory factor analysis. *Expected direction*: lower perceived vulnerability in settlements with greater forest cover and ecological connectivity (PH1).Bioeconomy Engagement Index (BEI): an ordinal variable (level 0 = no engagement; 1 = primary production; 2 = processing; 3 = processing + certification). This is an original indicator developed by the authors, grounded in literature on value-chain upgrading and socio-bioeconomy transitions. *Expected direction*: Higher values reflect greater involvement in bioeconomy value chains. This indicator will be used to examine whether higher engagement is associated with household income and with adoption of adaptation and mitigation practices (PH5).Reported Adaptive Capacity Index (RACI): a reflective score derived from farmers’ self-assessment of their ability to respond to climate impacts. The index is constructed as the average of Likert-scale items (range 1–5), where higher values indicate greater perceived adaptive capacity. Items draw on established adaptation assessment frameworks but were adapted to the Amazonian rural context. This indicator is used to examine associations proposed inPH4.

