Households with multigenerational demographic composition and participation in community organizations (PH3) will report higher adaptive capacity (as measured by the RACI), and this association will be supported by a more diversified portfolio of adaptation strategies (ASDI). This hypothesis is grounded in demo-livelihoods frameworks [32], which emphasize the role of intergenerational structures and social capital in shaping livelihood decisions and adaptive responses.

Secondary outcomes (exploratory measures to enrich analysis):

a) Adaptation Strategy Diversity Index (ASDI): a count-based index capturing the number and variety of adaptation practices reported by each household, including both traditional (e.g., collective work, soil management, water storage) and innovative strategies (e.g., improved seeds, irrigation systems, shade management). This is an author-developed indicator, conceptually grounded in livelihood and adaptation portfolio approaches widely used in climate adaptation research. The index reflects the breadth of a household’s adaptation repertoire, with higher values indicating a more diversified set of responses to climate impacts. The ASDI supports the examination of PH3 by providing a complementary measure of how demographic composition and social capital relate to adaptation strategy diversity.b) Municipal Climate Engagement Typology: a contextual variable (high, medium, or low engagement) constructed from a systematic analysis of municipal climate-related policies and budgets. The typology follows consolidated methodologies [33,34], combining two dimensions: (i) *policy engagement*, assessed through the presence, depth, and quality of municipal adaptation and mitigation plans (including objectives, instruments, and implementation mechanisms); and (ii) *budgetary engagement*, assessed through the classification and quantification of climate-relevant expenditures in municipal budgets. Municipalities are then categorized into high, medium, or low engagement based on their combined policy and budget scores (used to test HP4).

All outcomes will be operationalized on continuous, ordinal, or categorical scales, as appropriate, and incorporated into multilevel linear and generalized linear models (LMM/GLMM), with families (level 1) nested within settlements (level 2), which are nested within municipalities (level 3).

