#### Participant characteristics.

Participants include: (i) local public managers (1–3 per municipality), responsible for municipal policies on agriculture, environment, or rural development; (ii) community leaders (8–12 per settlement), invited to participate in focus groups, representing different social and productive segments; and (iii) settled families (up to 50 per settlement), covering a diversity of socioeconomic, productive, and demographic profiles. The study expects to include family farmers across different age groups, education levels, family compositions, and modes of engagement in local markets, as well as varying degrees of dependence on natural resources and participation in public policies. In each household, the respondent will be the adult member primarily responsible for agricultural and livelihood decisions (typically the main decision-maker), as this person is expected to have the most comprehensive knowledge of production, income sources, and climate-related impacts.

This sampling strategy seeks to balance territorial representativeness, social diversity, and logistical feasibility, enabling comparisons across municipalities, settlement types, and family profiles.

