#### Integration and triangulation.

In the final phase, the findings will be integrated following a sequential explanatory mixed-methods design (QUAN → QUAL) and a joint display triangulation framework [41]. The integration will be reported in accordance with the Good Reporting of a Mixed Methods Study (GRAMMS) framework and the Standards for Reporting Qualitative Research (SRQR) guidelines for the qualitative component.

A triangulation matrix will be constructed to systematically map convergences, complementarities, and divergences between quantitative, qualitative, and secondary data findings for each research objective and hypothesis. The matrix will define decision rules for interpreting relationships: (I) Convergence: Findings from different methods provide corroborating evidence for the same conclusion; (II) Complementarity: Findings from different methods elucidate distinct, non-overlapping aspects of a phenomenon, together providing a richer, more complete picture; (III) Discordance: Findings from different methods are contradictory or inconsistent. In such cases, we will re-examine the data and the assumptions of each method to propose potential explanations for the discrepancy (e.g., differences in perspective between managers and farmers, social desirability bias in surveys). (IV) Silence: An expected finding from one method is absent in the data from another method.

For example, a quantitative pattern of low adoption of a bioeconomy practice (QUAN) will be examined considering reported barriers in interviews (QUAL) and the (non)existence of supportive policies identified in secondary data. This synthesis will enable not only the identification of *what* occurs but also *why* and *how* adaptation and resilience processes unfold.

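### Field data may enter the municipal engagement typology before it is used to test PH4, and the stated order of analysis contradicts itself on this

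*Protocol article*

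**What the plan says.** Three parts of the protocol article bear on this.

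- **How the exposure is built.** The section on primary and secondary outcomes describes the typology as "constructed from a systematic analysis of municipal climate-related policies and budgets" and names it as the variable that tests the fourth hypothesis. The section on secondary data and municipal context analysis lists a plan quality score from content analysis, and adds that "a public expenditure audit, employing text mining of municipal transparency portals, will be conducted" to quantify climate-related budgets. Its next paragraph, on data-quality challenges, has all secondary data "triangulated with qualitative data from interviews and focus groups to ensure contextual accuracy". Its closing paragraph states that "the plan quality scores, and budget allocations will be combined to create a Municipal Climate Engagement Typology", which then enters the multilevel models.
- **What PH4 claims.** In Table 1, participatory municipal policies "are associated with higher adaptive capacity reported by communities and greater productive diversification based on socio-biodiversity". The outcome assigned to PH4 is RACI, a household score from farmers' "self-assessment of their ability to respond to climate impacts".
- **Who supplies the qualitative data, and when.** The participants include "community leaders (8–12 per settlement), invited to participate in focus groups". Under Phase 2, these groups discuss vulnerabilities and collective adaptation strategies. Municipal managers are interviewed on how policies are implemented. The data analysis plan and its general strategy put secondary data first, survey modelling second, qualitative analysis third and triangulation last.

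**The concern.** An exposure should be fixed without information related to the outcome. Here, a step described as a check on accuracy, drawing on leaders of the surveyed settlements, appears before the exposure is formed. The exposure leaves room for judgement: plan quality comes from content analysis, and spending is classified as directly or indirectly climate-related. If focus-group accounts sway that coding, and those accounts follow how capable the community feels, the typology carries part of the outcome it is meant to explain.

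PH4 has only 15 municipalities in three classes, so a few reclassifications can matter. There is also a consequence for the triangulation matrix, which defines "Convergence: Findings from different methods provide corroborating evidence for the same conclusion". If qualitative data have already been used to revise the secondary scores, part of the agreement between the two is built in, and some discordance is removed before it can be reported.

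**Working it through.** The protocol gives no figure to reproduce on this point. The check is a comparison of the text, followed by an illustration of size.

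**1. Order of steps.**

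| Place in the protocol article | Position of qualitative data |
|---|---|
| Secondary data and municipal context analysis | Used as a check on plan and budget data, described before the typology is formed and entered in the models |
| Data analysis plan; general strategy and integration | Analysed after the survey models; triangulation last |
| Phases 1 and 2 | Plan mapping and budget audit in Phase 1; interviews and focus groups in Phase 2 |

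The first row needs qualitative data before the models are fitted, and the second places them afterwards. If they come before, field views can enter the exposure. If they come after, the exposure can be revised once survey results are known. The document does not say which applies, or whether either is allowed to change a score.

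**2. Overlap of sources.** RACI comes from randomly sampled families. The focus groups are community leaders of the same settlements, and overlap of persons is neither stated nor excluded. Because the exposure is municipal, a shared local view is enough to link it to mean RACI.

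**3. Size, with no true PH4 effect.** Inputs from the protocol: 15 municipalities, three classes, 5% significance. Assumptions not in the protocol: equal classes, the correlation *r* between the focus-group view and mean municipal RACI, and the weight *w* that view receives.

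- Document score *s* and mean RACI *m* are independent N(0,1).
- Focus-group view *f* = *r·m* + √(1 − *r*²)·noise.
- Revised score = *s* + *w·f*, cut into thirds; two-sided linear trend test.

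| *w* | Municipalities reclassified | Rejection rate, *r* from 0.5 to 0.7 |
|---|---|---|
| 0 | 0 | about 5% |
| small | about 1 of 15 | 5.0–5.6% |
| 0.3 | about 2.9 of 15 | 7.4–9.3% |
| 0.5 | about 4.2 of 15 | 10.7–16.5% |

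The rows for *w* = 0.3 and 0.5 use 8,000 data sets per scenario, so the simulation standard error near 9% is √(0.093 × 0.907 / 8,000) ≈ 0.3 percentage points.

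**4. Second model, with sampling error in RACI.** This has 15 municipalities, 2 settlements each, 20 families per settlement, settlement ICC 0.05, municipal ICC 0.05 or 0.15, and 20,000 runs per cell. The score is (1 − *w*)·document + *w*·field signal, so *w* is on a different scale from step 3. Bias is High minus Low, in outcome SD.

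| *w* | *r* | Bias | Rejection rate |
|---|---|---|---|
| 0 | any | about 0 | 0.047–0.052 |
| any | 0 | about 0 | about 0.05 |
| 0.10 | 0.3 to 0.8 | +0.02 to +0.07 | 0.051–0.057 |
| 0.25 | 0.3 to 0.8 | +0.04 to +0.21 | 0.06–0.11 |
| 0.50 | 0.3 to 0.8 | +0.10 to +0.45 | 0.07–0.39 |
| 0.10 to 0.50 | −0.5 | −0.03 to −0.28 | 0.05–0.17 |

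The two models agree in pattern. Light use of field data does almost nothing, heavy use can matter, and the sign follows *r*.

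**The case against.** The strongest reply is that nothing in the document says a score will change. Both descriptions of the typology name only plans and budgets as scored components. Where the protocol sets rules for disagreement, in the triangulation matrix, discordance leads to proposed explanations and no rescoring is mentioned. RACI comes from another instrument and another class of participant, and managers, who supply half of the qualitative data, do not report RACI. Phase 1 precedes fieldwork. A contextual check could also improve the exposure by exposing plans that exist only on paper. Details such as coder blinding and lock dates commonly sit in a fuller document.

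Most of this stands, and it rules out some stronger readings.

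- A reader might infer that exposure and outcome are in fact dependent. The document shows shared places and an open path. It does not show that the path is used.
- A reader might infer a bias in favour of PH4. The sign depends on a correlation that the document does not give. If leaders in struggling places credit the municipality more, the bias runs against PH4.
- A reader might call the cross-check against transparency portals empty. That holds only for budgets, which are mined from those portals. For plan documents and for vulnerability indicators from other databases, the portals are a separate source.

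The reply does not remove the point. The issue is not a missing operational detail. The text puts a qualitative accuracy check ahead of the exposure it feeds, and contradicts its own sequence elsewhere. A check meant to secure accuracy ordinarily implies that something may be corrected.

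**Conclusion.** The point holds as an open path and a contradiction in sequence, not as a demonstrated bias. As written, information from the surveyed settlements may enter the PH4 exposure, and a reader of the results could not tell how far it had.

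The size depends on two unknowns: how many municipalities are reclassified, and how closely field views follow RACI. With assumed correlations of 0.5 to 0.7, the false-positive rate is about 5–6% for about 1 of 15 reclassified, 7–9% for about 3 and 11–17% for about 4. It is about 5% if nothing is rescored or if the field signal is unrelated to RACI. The built-in agreement in the triangulation matrix follows only if scores are revised in this way. The change is worth making because PH4 is a primary hypothesis and the remedy costs little.

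**What to change.** - Score the plan-quality measure, the budget measure and the resulting typology from Phase 1 documents alone. Lock them before any Phase 2 data from that municipality are seen, and use this version in the primary PH4 models.
- Use interviews and focus groups in the triangulation matrix, and report disagreement with the locked score there as discordance.
- Label any typology revised with field information a sensitivity analysis, and show it beside the primary result.
- Reconcile the section on secondary data and municipal context analysis with the order given in the data analysis plan and general strategy.

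The cost is protocol wording and a dated lock file in the planned repository. Phase 1 already precedes Phase 2, so no extra data are needed. In both simulation models the locked score keeps the false-positive rate at about 5% (0.047–0.052 in the second) with no bias on average. The downside is that errors in the documents, such as plans that exist only on paper, stay in the primary score and are addressed only in the sensitivity version.
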